#### ***n. 5.4 MHM Intervention Acceptability, Uptake, and Effectiveness (MAE) Sub-Study***

The CHIEDZA intervention will provide young women access to a choice of MHM products, analgesia, and education on pain management, menstruation, and MHM more generally. A prospective cohort sub-study will be nested within CHIEDZA to understand perceptions and practices around MHM and knowledge on menstruation and MHM, and to investigate the acceptability, uptake, and effectiveness of an informed MHM intervention aimed at providing access to MHM education, MHM product choice, and analgesia among young women.

##### ***i. 5.4.1 Background and Rationale***

The onset of puberty and menstruation is a fundamental experience for girls and women, and appropriate menstrual hygiene management (MHM) is directly linked with basic human rights. Yet, MHM continues to be a challenge for many girls and women, especially in LMICs. Due to a lack of access to appropriate education, affordable and accessible menstrual hygiene care products, and adequate sanitation, many women especially girls and young women during the first few years following menarche struggle to manage menstruation safely and/or with dignity. In LMICs, many girls and women have no access to clean water or private spaces to attend to their menstrual care needs and are forced to use non-absorbent, unhygienic, and uncomfortable materials that may negatively affect their health, education, and well-being. In 2012, the Joint Monitoring Program of the WHO and UNICEF defined adequate MHM as access to clean absorbents including, when relevant, sufficient washing, drying, storage and

wrapping of reusable absorbents; adequate frequency of absorbent change; washing the body with soap and water; adequate disposal facilities; and privacy for managing menstruation. Using the MHM definition as a measure, studies have shown that many girls and women in LMIC have inadequate MHM and inadequate MHM may hinder their daily activities, prevent girls and women from going to school or participating in income generating activities, or lead to stigma, discrimination, and adverse psychosocial outcomes. Options for menstrual health products include disposable and re-usable pads, tampons, period pants, and the menstrual cup. However, there are relatively few data on acceptability, uptake, and effectiveness of these products (especially reusable products which are more cost-effective and environmentally friendly) in LMICs. A study to investigate this will be nested within the CHIEDZA trial.

## ii. 5.4.2 Study Aim and Objectives

The aim of the MHM sub-study is to investigate the acceptability, uptake, and effectiveness of an MHM intervention within the community-based CHIEDZA trial among women aged 16-24 years.

The specific objectives are

1. To understand and describe the current knowledge levels, practices and perceptions around menstruation and MHM among women aged 16 – 24 years in Zimbabwe.
  2. To investigate menstrual product choice, continued use or discontinuation of products, and patterns of use over time among young women offered all 3 product choices
- Effectiveness
3. To investigate the effect of the intervention on MHM practices e.g. access and use of clean absorbents, sufficient washing, drying, storage and wrapping of reusable absorbents; washing the body with soap and water
  4. To investigate the effect of the MHM intervention on the knowledge and perception of menstruation and MHM
  5. To investigate the effect of the MHM intervention on pain management during menstruation

### Acceptability

6. To investigate the acceptability of the intervention in a community-based SRH intervention programme i.e. intervention uptake, affective attitude, burden, ethicality, intervention coherence, opportunity costs, perceived effectiveness, self-efficacy, and intervention implementation challenges, fidelity, reach, and service quality

Objective 1 will be met by using CHIEZDA data and by carrying out qualitative data research with female CHIEDZA participants that uptake MHM services. Quantitative data collected from the nested cohort will also contribute to objective 1. Objectives 3-6 will be met by carrying out qualitative and quantitative data research within the nested cohort study.

### iii. 5.4.3 Theory of change

A theory of change model has been developed to illustrate the expected outcomes and impact from the MHM sub-studies (Figure 5).

### iv. 5.4.4 MHM Intervention

All CHIEDZA attendees will have *a choice of one of the following MHM products*: the menstrual cup or reusable pads. This will be accompanied by analgesia (12 tablets of paracetamol or ibuprofen), a bar of soap, a simple period-tracking sheet, and comprehensive MHM education including an MHM educational pamphlet participants can take home and an MHM educational video to be played at the CHIEDZA centre. Clients will be able to ask for a different product but only after 1) a minimum of 3 months of usage and all CHIEDZA female participants who choose an MHM product will have the option of changing their chosen MHM product if they bring the existing MHM product back to the CHIEDZA centre.

Participants in the nested cohort study will be given comprehensive MHM education including an MHM educational pamphlet participants can take home and an MHM educational video to be played at the CHIEDZA centre, a monthly supply of up to 12 analgesics (ibuprofen or paracetamol), a comprehensive period tracking diary, and *all the MHM products* as summarised in Table 5. Participants in the cohort will be recruited from 2 randomly-selected CHIEDZA intervention clusters in Harare and will be followed-up 3 monthly for one year. At enrolment, the 6 month, and 12 month visit, participants will be required to self-complete a questionnaire (using Open Data Kit on a tablet) and at the 3 month and 12 month (endline) visit, participants will be required to hand-in their period tracking diary for review.

**Figure 5: Theory of Change model for the MAE sub-study**

[figure not shown]

**Table 5: MHM Intervention**

| MHM Product   | Hardware                                                                                                                                                                                                                                                                                         | Software                                                                                                                                                                                                                         |
|---------------|--------------------------------------------------------------------------------------------------------------------------------------------------------------------------------------------------------------------------------------------------------------------------------------------------|----------------------------------------------------------------------------------------------------------------------------------------------------------------------------------------------------------------------------------|
| Menstrual Cup | 
 
• 1 cup
 
• 1 pack of disposable pads (1 month supply)
 
• 2 pairs of underwear
 
• Soap
 
• MHM educational pamphlet
 
• Pain medication
 
                                                                   | 
 
• Initial education session: 
 
– One-on-one product demonstration
 
– Pain management information
 
 
 
                      |
| Reusable Pads | 
 
• 1 pack of reusable pads (AFRIPads with 4 reusable pads/pack or Days for Girls with 2 period shields and 8 period liners/pack)
 
• 2 pairs of underwear
 
• Soap
 
• MHM educational pamphlet
 
• Pain medication
 
 | 
 
• Scheduled education sessions throughout intervention period that explore myths and taboos and elaborate on puberty, menstruation, and menstrual hygiene
 
• MHM Video
 
 |

#### v. 5.4.5 Study Outcomes

**Objective 1:** *To understand and describe the current knowledge levels, practices and perceptions around menstruation and MHM among women aged 16 – 24 years in Zimbabwe.*

**Outcome 1:** Qualitative data from the FGDs and descriptive data from the quantitative questionnaire will be analysed with proportion and cross-tabulations to show the distribution of knowledge, perceptions, and practices regarding MHM. Data from the FGDs will complement the quantitative data.

**Objective 2:** *To investigate menstrual product choice, continued use or discontinuation of products, and patterns of use over time among young women offered all 3 product choices*

**Outcome 2:** Menstrual product choice over time amongst young women and proportion of young women with continued or discontinued menstrual product use over time. Data from the FGDs and IDIs will complement the quantitative data

**Objective 3:** *To investigate the effect of the intervention on MHM practices e.g. access and use of clean absorbents, sufficient washing, drying, storage and wrapping of reusable absorbents; washing the body with soap and water*

**Outcome 3:** Using the quantitative data collected from the period tracking diary entries and the pre- and post- quantitative questionnaires, the self-reported MHH practices will be used to generate a pooled, aggregate of adequate MHM practice consistent with the definition given by the WHO and UNICEF and the theory of change model

developed for the longitudinal cohort sub-study intervention. Data from the FGDs and IDIs will complement the quantitative data

**Objective 4:** *To investigate the effect of the MHM intervention on the knowledge and perception of menstruation and MHM*

**Outcome 4:** Pre- and post-intervention quantitative data from the questionnaires will be used to analyse change in the proportion of cohort participants with improved MHM knowledge and perceptions over time

**Objective 5:** *To investigate the effect of the MHM intervention on pain management during menstruation*

**Outcome 5:** Data collected from the period tracking diary and the pre- and post-intervention questionnaires will be used to analyse change in pain management in cohort participants.

**Objective 6:** To investigate the acceptability of the intervention in a community-based SRH intervention programme i.e. intervention uptake, affective attitude, burden, ethicality, intervention coherence, opportunity costs, perceived effectiveness, self-efficacy, and intervention implementation challenges, fidelity, reach, and service quality

**Outcome 6:** An assessment of MHH intervention acceptability i.e. affective attitude, burden, ethicality, intervention coherence, opportunity costs, perceived effectiveness, self-efficacy, and intervention implementation challenges, fidelity, reach, and service quality, using quantitative data on MHH intervention uptake and a qualitative data assessment from participants and the intervention team

#### **vi. 5.4.6 Data from the CHIEDZA intervention**

##### ***Quantitative Methods***

Quantitative data from all female participants that accessed MHM services across the 12 CHIEDZA intervention clusters will be used to generate yield data on MHM intervention uptake (Objective 6) and MHM product choice over time (Objective 2). MHM product choice over time will be assessed using data from SIMPRINTS biometric system which will record every time an existing female CHIEDZA participant returns an MHM product of choice and requests to uptake a different MHM product (Objective 2).

Cross-tabulation tests will also be run to assess the association between some socio-demographic variables such as age with MHM intervention uptake and MHM product choice. Informing factors and reasons for MHM intervention uptake and changes in MHM product choice will then be further explored qualitatively within the two randomly selected nested MHM sub-study intervention clusters from the CHIEDZA intervention province of Harare.

### ***Qualitative Methods***

Up to 12 FGDs will take place throughout the delivery of the intervention with at least 2 FGDs in each of the nested MHM sub-study intervention clusters at baseline, 6 months, and 12 months. A purposive sample of 12 – 15 participants will be selected to participate in FGDs to include those of varying ages, females using different types of MHM products, and females that have changed their MHM product of choice over time. Written informed consent will be obtained from each participant before the FGDs.

The FGDs will be conducted by local female qualitative research assistants in either Shona, Ndebele or English (as agreed by the participants) and will be audio recorded. Each discussion is expected to take between 1 – 2 hours. Discussions will use semi-structured topic guides to explore current knowledge on menstruation and MHM and practices and perceptions around MHM (Objective 1). The FGDs will also be used to investigate the factors that may inform product choice and continued or discontinued menstrual product use over time (Objective 2) and the acceptability of an MHH intervention within CHIEDZA (Objective 6). These FGDs will be followed-up with IDIs to further explore individual views on menstrual product choice and use over time. Descriptive narratives, from participant observations at the CHIEDZA sites, will also be used to assess MHH intervention fidelity and service delivery quality (Objective 6)

Throughout the delivery of the intervention, some of the FGD participants may be invited for a follow-up IDI. Up to 10 IDIs may take place and qualitative data from these interviews will be used to complement the data from the FGDs. Written informed consent will be obtained from each participant before the IDIs.

Audio recordings of the FGDs and IDIs will be transcribed verbatim and then translated (if applicable) into English for analysis. Thematic analysis and coding of emerging themes (common and divergent) will be conducted by 2 social science research assistants independently. Regular data analysis team meetings steered by a senior social scientist will be held to discuss and compare the work of the RAs. All recordings will be downloaded on to a password-secured laptop for processing purposes and then deleted once the nested cohort study is completed.

#### **vii. 5.4.7 The Nested MHM Cohort Sub-Study Intervention**

##### ***MHM Sub-Study Pilot***

At the start of the trial, the tools and procedures will be piloted for the nested cohort study. In addition, qualitative research will be carried out to gain a better understanding of how participants experienced the MHM component during the pilot phase. The qualitative research during the pilot phase will include up to 2 FGDs (one each with young girls (16 – 20 years old) and older girls (21 – 24 years old)) with a purposive sample of 12 – 15 participants to include those of varying

ages and those using different MHM products. Tools and procedures will be revised based on the results and experiences of the pilot.

### ***Recruitment***

Two CHIEDZA intervention clusters from Harare district will be randomly selected for the cohort sub-study. Using convenience sampling, the first three hundred (combined) female CHIEDZA participants seeking MHM services in the selected clusters will be recruited for the cohort and followed for 1 year. Eligible young women who express an interest in enrolling in the cohort will be given information about the study and will be provided the opportunity to ask questions. Inclusion criteria will be willingness to participate and the ability to provide signed informed consent. Exclusion criteria will be the following: current pregnancy or intending to get pregnant within the next 1 year; irregular or absent bleeding within the last 3 months; or having any condition that, in the opinion of the investigator, would preclude informed consent or make study participation unsafe. After all questions have been answered, eligible young women will be asked to sign a consent form. Participation in the cohort will be optional and it will be emphasized that care of those who decline to participate will not be adversely affected. Participants will also be allowed to withdraw at any time and will not be adversely affected.

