### ***Enrolment***

At enrolment, consenting participants will receive the MHM intervention including MHM education, analgesics, 2 pairs of period pants, and all the MHM products in Table 5. Participants will also be asked to complete a self-administered structured quantitative questionnaire using ODK on a tablet to obtain data on socio-demographics, and genital and menstrual hygiene, knowledge on menstruation and MHM, MHM perceptions and practices, pain management, and psycho-social well-being. Each participant will also be given a comprehensive 4 month period tracking diary. The participants and RAs will also go through the participants' period tracking diaries together to make sure participants are comfortable and confident using the diaries and that the diaries are being completed accurately on a monthly basis.

Participants will also be given a participant booklet with the dates of their follow up visits (with a two-week window period around their scheduled follow-up visit date). If participants fail to attend their CHIEDZA site visit, they will be contacted and asked if they can be visited at home.

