### ***Sample Size***

A sample size is based on Objective 3: 300 participants will provide 90% power to detect an increase in adequate HM practices from 10% to a double of 20% before (pre-) and after (post-) the intervention for each sub-study participant respectively.

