### ***Statistical Methods***

Descriptive statistics will be used to show the socio-demographic characteristics as well as the distribution of knowledge, perceptions and practices regarding MHM. The self-reported MHM practices will be used to generate a pooled, aggregate of adequate MHM modified from the Joint Monitoring Program of the WHO and UNICEF in 2012. The MHM sub-study intervention will only affect three components of the definition: access to clean absorbents including, when relevant, sufficient washing, drying, storage and wrapping of reusable absorbents; adequate frequency of absorbent change; and basic understanding of menstruation. The intervention will not affect washing the body with soap and water; adequate disposal facilities; or privacy for managing menstruation.

McNemar's test for correlated proportions and conditional logistic regression will be used to compare the proportion with improved MHM practices (Objective 3), proportion with good knowledge and appropriate perceptions (Objective 4), and appropriate pain management (Objective 5) pre- and post- the intervention.

Data from all of the period tracking diary entries will be used for descriptive statistics on MHM product choice and continued or discontinued product use over time, and MHM product patterns of use, MHM practices and pain management during menstruation (Objectives 2, 3, and 5). The diary entries will also track if participants missed work or school on the days before, after, or during their periods.

The facilitators, barriers, reasons for MHM product choice and continued and discontinued use of products over time and an appraisal of MHM products from participants will be further explored using qualitative methods.

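### The MHM cohort does not exclude women who already received MHM products or education from CHIEDZA, so its 'pre' value may be contaminated, and its uncontrolled change should not be called an effect

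*Combined protocol and SAP*

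**What the plan says.** **Recruitment (5.4.7).** Two Harare intervention clusters are drawn at random, and "the first three hundred (combined) female CHIEDZA participants seeking MHM services in the selected clusters will be recruited for the cohort". Inclusion needs only willingness and signed consent. The exclusions cover pregnancy or planned pregnancy, irregular or absent bleeding, and conditions that would preclude consent or make participation unsafe. Earlier MHM products or education from CHIEDZA appear in neither list.

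**Ordinary service (5.4.4).** Outside the cohort, CHIEDZA attendees may choose a cup or reusable pads, with analgesia, soap, a tracking sheet, a pamphlet and education that includes "an MHM educational video to be played at the CHIEDZA centre". Section 2.3 also describes a three-month pilot in one Harare trial cluster, and 5.4.7 refers to women's experience of the MHM component in that pilot.

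**Enrolment (5.4.7).** "At enrolment, consenting participants will receive the MHM intervention including MHM education, analgesics, 2 pairs of period pants" and the products in Table 5. The next sentence adds the questionnaire, joined by 'also'.

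**Objectives, outcomes and analysis.** Objectives 3 to 5 (5.4.2) ask for the effect of the intervention on practices, on knowledge and perceptions, and on pain management. Outcome 4 (5.4.5) reads "Pre- and post-intervention quantitative data from the questionnaires will be used to analyse change in the proportion of cohort participants" with improved knowledge and perceptions. Under Statistical Methods, "McNemar's test for correlated proportions and conditional logistic regression will be used to compare the proportion with improved MHM practices", with knowledge, perceptions and pain management treated in the same way. No comparison group is planned.

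**Sample size (5.4.7).** The calculation is made for Objective 3 and claims that "300 participants will provide 90% power to detect an increase in adequate HM practices from 10% to a double of 20" per cent. The two proportions are to be taken within person, that is, "before (pre-) and after (post-) the intervention for each sub-study participant respectively".

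**The concern.** A before-after comparison needs a 'before' that precedes exposure. Here the recruiting ground is the same service that already supplies MHM products and education, and nothing in the criteria keeps out women who have had them. Each such woman brings some of the intervention into her enrolment answers. That raises the 'pre' proportion and shrinks the change that McNemar's test is meant to detect. Earlier product use bears mainly on practices and pain management (Objectives 3 and 5). Earlier education bears mainly on knowledge and perceptions (Objective 4).

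The second difficulty is attribution. Pairing removes fixed differences between women, but not what changes over a year. The recruits currently seek MHM services, they answer the same questionnaire at enrolment, 6 and 12 months, and the protocol itself records COVID-19 disruption. Any of these could move the result. The sub-study would then report an effect that its design cannot separate from other change.

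**Working it through.** **Inputs.** From Sample Size in 5.4.7: n = 300, 10% before, 20% after, 90% power, paired. That paragraph does not state alpha, within-person correlation or dropout. Assumed here: two-sided 0.05 and independent paired responses.

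**Formulas.** Discordant cells under independence: p10 = p_pre(1 − p_post) and p01 = (1 − p_pre)p_post. Let ψ = p10 + p01 and δ = p_post − p_pre.

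- Power = Φ[(δ√n − 1.96√ψ)/√(ψ − δ²)]
- n = [1.96√ψ + 1.2816√(ψ − δ²)]²/δ² for 90% power

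**Step 1: the plan's own figure.** p10 = 0.10 × 0.80 = 0.08 and p01 = 0.90 × 0.20 = 0.18, so ψ = 0.26 and δ = 0.10.

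- n = (1.96 × 0.5099 + 1.2816 × 0.5)²/0.01 = 269 complete pairs. Allowing 10% loss, 269/0.9 = 299, which agrees with 300.
- Power with all 300 = Φ[(1.732 − 0.999)/0.5] = Φ(1.465) = 92.9%.

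The stated size is therefore reproduced under plausible, though unstated, assumptions.

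**Step 2: carry-over (illustration only).** Suppose a share s of recruits already stands at 20% at enrolment. Then p_pre = 0.10 + 0.10s and the apparent gain is 10(1 − s) points.

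| s | p_pre | gain (points) | ψ | power, n = 300 |
|---|---|---|---|---|
| 0 | 10% | 10 | 0.260 | 92.9% |
| 10% | 11% | 9 | 0.266 | 86.0% |
| 20% | 12% | 8 | 0.272 | 76.0% |

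For s = 20%: Φ[(0.08 × 17.32 − 1.96 × 0.5215)/√(0.272 − 0.0064)] = Φ(0.705) = 76.0%.

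Partial carry-over costs less. If 20% of recruits were only halfway, at 15%, then p_pre = 0.8 × 0.10 + 0.2 × 0.15 = 11% and power is 86.0%, not 76.0%.

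**Step 3: setting the exposed women aside.** If 10% of 300 had prior receipt and were left out, 270 pairs remain at 10% to 20%, with power 90.1% (against 86.0% if kept). At 20%, 240 pairs remain, with power 86.4% (against 76.0% if kept). Under full carry-over, exclusion therefore costs less power than dilution. With the half carry-over of step 2 the two are about equal (86.4% against 86.0%).

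**Step 4: no comparison group (illustration only).** With no intervention effect, but a background rise from 10% of 2, 3 or 5 points, the chance of a significant increase at n = 300 is 11.9%, 20.9% or 45.5%. A background fall would mask a real gain instead. A larger sample cures neither problem.

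**The case against.** Several counter-arguments have force.

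- **Prior exposure is inferred from silence.** 'The first three hundred' could mean women at first contact, and a woman who never sought MHM services has not received a product. This stands as a caution. But no section says first contact, and the criteria as written admit repeat clients.
- **Visit order.** A reader might infer from the Enrolment paragraph that education is given before the baseline questionnaire. The text does not support that. It is a list joined by 'also', and other sections speak of baseline and of before and after. It is an ambiguity. Same-visit education could colour knowledge and perception answers, but could hardly change past absorbent use.
- **Size of the loss.** The share s has no source, and full carry-over is close to a worst case. The ordinary service offers one product, while the cohort receives all products, a monthly analgesic supply and a fuller diary. This is accepted, and the figures are illustrations.
- **Direction of bias.** A reader might infer that practices would have improved anyway. The documents support only that they could change. COVID-19 restrictions, for example, could have worsened them.
- **The randomised endline survey.** It might seem to supply the missing control. Its MHM outcome (7.1) measures the whole CHIEDZA package at ages 18 to 24. It includes body washing, privacy and disposal, which Statistical Methods in 5.4.7 says the MHM intervention will not affect, and 7.1 lists no outcome for menstrual knowledge or pain. It cannot stand in for Objectives 3 to 5.
- **Importance.** This is an openly described before-after, mixed-methods sub-study outside the trial's primary and secondary objectives. That limits the weight of the point but does not remove it.

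**Conclusion.** The point holds in a limited form. Applied as written, the eligibility rule lets previously exposed women into a comparison labelled pre- and post-intervention, and their presence would shrink the measured change. Power would fall from 93% to 86% or 76% if 10% or 20% of recruits had full carry-over. This rests on independent pairs, two-sided 5% and a share that the documents do not give.

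It does not follow that the sample size is miscalculated: 300 and 90% are reproducible. Nor can the net bias be signed, because carry-over pulls the change down while time trends and repeat testing could push either way. Without a comparison group, the observed change cannot be attributed to the intervention. The HIV primary outcome is not touched. This is an inexpensive improvement to a nested sub-study.

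**What to change.** In 5.4.7, with matching wording in 5.4.2 and 5.4.5:

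1. Exclude women who have previously received MHM products or MHM education from CHIEDZA, including during the pilot, established by a screening question at enrolment. The data team may confirm the answer. Service staff cannot do so under the present rules, because 6.1.2 limits what they see of earlier visits to HIV status, date of last HIV test and red flag, and 6.1.1 makes fingerprints optional. At minimum, record prior receipt and make never-exposed women the primary pre-post analysis set.
2. As a clarification, state that the enrolment questionnaire is completed before the education session and the handing over of products. This matters mainly for Objective 4.
3. Word Objectives 3 to 5 and their outcomes as within-person change rather than effect. Cite the endline MHM outcome only as the effect of the whole CHIEDZA package on MHM in 18 to 24 year olds.

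**Cost.** One eligibility line with a screening question, one sentence on visit order, and rewording. Recruitment of 300 may take longer because repeat MHM clients are not eligible. Under the fallback, the primary analysis set is smaller than 300 by the number previously exposed.
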